#### Statistical considerations and analysis population

Analysis populations included the intention-to-treat (ITT) population, the modified intention-to-treat population and the per-protocol population. The ITT population includes all participants undergoing randomisation. The mITT population is defined as participants who undergo randomisation and had a culture positive for *Mycobacterium tuberculosis* collected at baseline or within two weeks of randomisation, excluding those with baseline isolates susceptible to rifampicin based on phenotypic DST. Additionally, for the mITT analysis, participants in Group A with fluoroquinolone-resistant baseline isolates confirmed with phenotypic DST will be excluded. Conversely, those in Group B with fluoroquinolone-susceptible isolates will be excluded. Participants who undergo randomisation in error or do not receive any study treatment after randomisation are also excluded from the mITT population. The PP population is derived from the mITT population, excluding those with inadequate treatment, defined as having completed less than 80% of the prescribed doses within 120% of the planned duration. Participants who discontinue treatment due to treatment failure, adverse events, or death will not be excluded from the PP population. Safety analyses will be conducted in the safety population, which includes all participants who receive at least one dose of the study regimen, and will be analysed according to the treatment actually administered.

The primary efficacy analysis will be conducted in the mITT population, and efficacy outcomes will be reported as supportive analyses from both the PP and ITT populations. The absolute between-group difference with 95% confidence interval (CI) in the proportion of participants with a favourable outcome will be calculated. The non-inferiority of an experimental arm versus the control arm will be established if the upper bound of the 95% CI is less than 10% (the margin of non-inferiority). In group A, multiple experimental arms are compared to the control regimen. Type I error rate will be controlled with a pre-planned fixed sequence method. First, the regimen with the highest expected treatment success rate will be compared to the control. If non-inferiority is established, comparisons will proceed sequentially to the next experimental regimen in descending order of expected efficacy. For any regimen that demonstrates non-inferiority, a subsequent test for superiority over the control will be performed.

Patient characteristics will be described with median and range (or interquartile range), or numbers and percentages. The median time to smear and culture conversion will be estimated in each arm using the Kaplan-Meier method and between-group difference will be compared with the log-rank test. Proportion of participants with any grade 3–5 adverse event, any serious adverse event (SAE) and any treatment-related SAE will be described with numbers and percentages.

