#### In participants resistant to fluoroquinolones

Pre-XDR TB participants are identified with the Xpert MTB/XDR assay prior to treatment initiation. The experimental arm is a 9-month regimen consisting of bedaquiline, cycloserine, clofazimine, linezolid and pyrazinamide. Treatment could be extended to 11 months if cavities are present at month 9 or in case of a positive culture at month 2. Pyrazinamide will be discontinued from the study regimen if baseline WGS results reveal pyrazinamide resistance.

The comparator is a conventional longer regimen consistent with the national guidelines [11], including bedaquiline, cycloserine, clofazimine and linezolid. Treatment duration is 20 months, with a 6-month intensive phase and a 14-month continuation phase. Composition of the study regimen and dosing is described respectively in Tables 1 and 2.

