^*^ Sputum rapid molecular test for rifampicin resistance should be performed during screening for eligibility assessment, and rapid molecular test for fluoroquinolone resistance should be acquired before randomisation for stratification

^**^ Timepoint of EOT in Regimen A1, A2, A3, A4, A5 and B1 is 9 months. Timepoint of EOT in Regimen B-SOC is 20 months

^#^ Timepoint of EOS is 21 months after randomisation

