**Unfavourable outcome**: (1) At least one of the last two cultures (taken from respiratory samples collected on separate visits at least 7 days apart) is positive and laboratory cross contamination is ruled out. The latest between month 21 and month 23. (2) There is no culture result collected between month 21 and 23 or the result is positive due to laboratory cross contamination; and - bacteriological, radiological and clinical evaluation is unfavourable. OR - the most recent culture result is positive in the absence of laboratory cross contamination. (3) There is no culture result collected between month 21 and 23 or the result is positive due to laboratory cross contamination; and - either there is no other post-baseline culture result, or the penultimate culture result is positive due to laboratory cross contamination. OR - bacteriological, radiological and clinical evaluation is not available. (4) The last culture result (from a respiratory sample collected between month 21 and 23) is negative; and either there is no other post-baseline culture result, or the penultimate culture result is positive due to laboratory cross contamination; and bacteriological, radiological and clinical evaluation is unfavourable. (5) The last culture result (from a respiratory sample collected between month 21 and 23) is negative; and either there is no other post-baseline culture result, or the penultimate culture result is positive due to laboratory cross contamination; and bacteriological, radiological and clinical evaluation is not available. (6) Participant whose treatment regimen needed to be terminated or permanently changed ^a^ to a new regimen. (7) Treatment extension that does not meet protocol-defined extension criteria. (8) Initiation of a new RR-TB treatment regimen after the end of the allocated study regimen and before month 21 (relapse). (9) Loss to follow-up ^b^. (10) Death from any cause.

^a^ A permanent regimen change is constituted by any of the following: [1] adding or replacing two or more drugs in the allocated regimen; [2] adding second-line injectables in the allocated regimen; [3] replacing a group C drug with a group B drug (clofazimine, cycloserine) not originally included; [4] replacing a group B drug with a group A drug (moxifloxacin, levofloxacin, linezolid, bedaquiline) not originally included

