^b^ Loss to follow-up is defined in case that a participant fails to complete two or more consecutive scheduled visits and cannot be reached after at least three phone calls and one home interview

Main secondary outcomes are measured in fluoroquinolone-susceptible and fluoroquinolone-resistant arms respectively. Secondary outcomes are defined as follows:

Time to sputum smear conversion in the mITT population.Time to sputum culture conversion in the mITT population.The proportion of participants with a favourable outcome at 21 months post-randomisation in the per-protocol (PP) population.The proportion of participants with grade 3 or higher adverse event (AEs), serious adverse events (SAEs) at 21 months post-randomisation in the safety population.All-cause mortality and treatment relevant mortality at 21 months post-randomisation in the safety population.The proportion of participants with treatment relevant SAEs at 21 months post-randomisation in the safety population.The proportion of participants with grade 3 or higher QTc prolongation in the safety population.The proportion of participants experiencing permanent drug discontinuation or replacement due to QTc prolongation in the safety population.

Exploratory outcome measures are defined as the following:

The proportion of participants with a favourable outcome at 21 months after randomisation in regimen A2a, A2b and A2c in the mITT population.The proportion of participants with grade 3 or higher myelosuppression, peripheral neuropathy and optic neuropathy in regimen A2a, A2b and A2c in the safety population.The proportion of participants with linezolid discontinuation or dose reduction due to AE in regimen A2a, A2b and A2c in the safety population.

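### In Group B the per-protocol rule keeps mid-course losses to follow-up as failures in B1 but removes them from B-SOC, which tilts the supportive comparison against B1

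*Protocol article*

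**What the plan says.** All references are to the protocol article.

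- **PP rule** (Statistical considerations and analysis population). PP is the mITT population "excluding those with inadequate treatment, defined as having completed less than 80% of the prescribed doses within 120% of the planned duration". One protection follows: "Participants who discontinue treatment due to treatment failure, adverse events, or death will not be excluded from the PP population". Loss to follow-up and voluntary withdrawal are not in it.
- **Planned durations** (In participants resistant to fluoroquinolones). For B1: "The experimental arm is a 9-month regimen consisting of bedaquiline, cycloserine, clofazimine, linezolid and pyrazinamide". An extension is possible: "Treatment could be extended to 11 months if cavities are present at month 9 or in case of a positive culture at month 2". For B-SOC: "Treatment duration is 20 months, with a 6-month intensive phase and a 14-month continuation phase". The Table 3 footnotes agree: "Timepoint of EOT in Regimen B-SOC is 20 months".
- **Outcome** (Outcome measurements, Table 4). The unfavourable list ends with "9) Loss to follow-up ^b^. (10) Death from any cause". Footnote b counts as lost a participant who "fails to complete two or more consecutive scheduled visits and cannot be reached after at least three phone calls and one home interview". An unfavourable classification made earlier rules out a favourable one.
- **Visits** (Follow-up duration and participant timeline, Table 3). Visits are monthly on treatment. After B1 treatment they fall at months 12 and 15 and at end of study, month 21.
- **Role of PP.** The PP favourable rate is a listed secondary outcome. The primary analysis is mITT, and PP and ITT are both supportive.

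**The concern.** The exclusion is tied to a share of the planned course, and in Group B one course is more than twice as long as the other. The same loss to follow-up, at the same time since randomisation, can then be a retained failure in B1 and an exclusion in B-SOC. Removing failures from one denominator only raises that arm's success rate, so PP can favour B-SOC even when the regimens perform alike.

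At stake is how PP is read beside mITT. If the two disagree in Group B, the reader cannot tell whether adherence or regimen length explains it.

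**Working it through.** **Plan's own figure.** For Group B: 65% versus 75%, margin 10 points, one-sided alpha 0.025, 80% power. n = (1.960 + 0.842)² × (0.65×0.35 + 0.75×0.25) / (0.10 + 0.10)² = 7.849 × 0.415 / 0.04 = 81.4, so 82 per arm, as stated. 82/0.70 = 117.1, against the stated 117. The planning figures are not in question; they give the scale for the shift below.

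**Step 1: where the 80% mark falls**, with full adherence until departure.
- B1: 0.8 × 9 = 7.2 months (0.8 × 11 = 8.8 if an extended course counts as planned).
- B-SOC: 0.8 × 20 = 16 months.

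**Step 2: a participant lost at month 10.**
- B1: 9/9 = 100% of doses (10/11 = 91% if extended). Stays in PP, misses months 12 and 15, cannot be reached, and is unfavourable as lost to follow-up.
- B-SOC: 10/20 = 50% of doses. Not protected, so removed from PP.

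**Step 3: when a retained participant can still meet footnote b.**
- B1: two consecutive visits can be missed only by leaving before month 15 (missing months 15 and 21). Window 7.2 to 15, or 7.8 months.
- B-SOC: visits are monthly to month 20, then month 21, so the latest departure that misses two is just before month 20. Window 16 to 20, or 4 months.

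**Step 4: size.** Assumptions, none of them in the documents: constant monthly loss rate h, equal in both arms, and 85% success among those not lost. Among participants past the 80% mark, the share retained as lost is 1 - exp(-7.8h) in B1 and 1 - exp(-4h) in B-SOC. The shift is -0.85 × the gap.

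| h per month | B1 retained losses | B-SOC retained losses | Gap (points) | Shift in PP difference (points) |
|---|---|---|---|---|
| 0.5% | 3.8% | 2.0% | 1.8 | -1.6 |
| 1.0% | 7.5% | 3.9% | 3.6 | -3.0 |
| 1.5% | 11.0% | 5.8% | 5.2 | -4.4 |

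The reference is a PP difference of zero, which this model gives when such losses are excluded in both arms.

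**Plausibility.** Under the same assumptions B1's overall favourable rate is 0.85 × exp(-15h) = 78.9%, 73.2% or 67.9%. The planning value is 75%, so the 1.5% row sits least comfortably with the protocol.

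**The case against.** **A larger shift.** A reader might count every B1 departure up to month 21 as a failure. The windows become 13.8 and 5 months, the retained losses 6.7%, 12.9%, 18.7% versus 2.5%, 4.9%, 7.2%, and the shifts about -3.6, -6.8 and -9.8 points, the last close to the 10-point margin. The documents do not support this as the general case. A B1 participant who leaves after month 15 misses one scheduled visit and is not lost under footnote b. With a negative last culture and a favourable evaluation, that participant is favourable under Table 4. The outcome would be unfavourable only if, for instance, the evaluation were unavailable.

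**Direction is not uniform.** B1 participants who withdraw but can still be reached may be favourable. B-SOC participants removed for poor adherence may include some who would have been favourable, and removing them lowers the B-SOC rate. Both points stand and offset part of the shift; the documents do not allow the amount to be estimated.

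**The two losses differ.** One participant finished the allocated course and the other took half, which an adherence-based set is meant to separate. That justifies keeping the stated PP set, but not reading its between-arm difference without a companion analysis.

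**Reading of prescribed doses.** If it means doses prescribed up to departure, the B-SOC participant could stay in PP. The reference to planned duration favours the full-course reading, but the text does not settle it.

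**The 120% window.** For B-SOC, 1.2 × 20 = month 24, after end of study. A reader might infer that adherence cannot be judged. In practice, reaching 16 months of doses only after month 21 needs about five months of interruption, so this has almost no effect.

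**Conclusion.** The point holds for the supportive PP comparison in Group B. As written, and on the full-course reading, losses to follow-up between about month 7.2 and month 15-16 count as failures in B1 and are absent from B-SOC. The shift against B1 is about -1.6 to -4.4 points for assumed losses of 0.5% to 1.5% per month, before the offsets. Its size rests on the assumed loss rate, equal in both arms, and on 85% success otherwise.

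A reader might infer that the B1 non-inferiority claim is itself at risk. The documents do not support that. The primary analysis is mITT, which has no adherence exclusion; no stated decision depends on PP; and a bias against B1 cannot create a false claim of non-inferiority. The harm is a secondary outcome, and a possible PP-mITT disagreement, that regimen length alone could produce.

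**What to change.** 1. Keep the stated PP set.
2. State that prescribed doses means the full planned course.
3. For Group B, also report a PP analysis in which loss to follow-up is handled by one rule, timed from randomisation, in both arms: all such losses retained as unfavourable. As a complement, exclude all such losses before month 21 in both arms. The complement should not replace the PP set, because it drops B1 participants who took every dose and were lost afterwards.
4. Time each loss by last contact since randomisation. The two-visit test can be met until month 15 in B1 but until month 20 in B-SOC, so visit spacing alone does not give a common clock.
5. Interpret any PP-mITT disagreement in Group B in light of these analyses.

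The cost is a sentence of definition and a little more analysis work. No new data are needed, and the change is best made before database lock.

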#### Sample size assumptions

The sample size calculation was performed in PASS 11 system (NCSS, Version 11.0.10). In an individual patient data meta-analysis of 13,273 MDR/RR-TB patients from 38 countries, the treatment success rate of the bedaquiline-containing oral shorter regimen is 73% [16]. We thus assume a 70% favourable rate in the control arm and 80% in the experimental arms in fluoroquinolone susceptible patients. Since multiple experimental groups are simultaneously compared with the control group, the family-wise type I error will be controlled by a fixed sequence approach. The experimental groups are tested sequentially in a pre-specified order, and if any group fails to demonstrate non-inferiority, testing for subsequent groups will be discontinued. All the previous comparisons will be done at the one-sided alpha level of 2.5%. Therefore, a sample size of 73 per arm will afford 80% power to establish non-inferiority of seven experimental regimens with a non-inferiority margin of 10% at a one-sided α level of 2.5%. The number excluded from the modified intention-to-treat population is estimated to be 30% and therefore the recruitment target is increased to 104 per arm. The total sample size of fluoroquinolone-susceptible RR-TB participants is 832.

By November 2024, randomisation to regimen A2b, A2c as well as A5 has been ceased following protocol amendment. The actual number of enrolled participants at the time of early closure were 73, 72, 92 respectively in regimen A2b, A2c and A5. Therefore, the total sample size of fluoroquinolone-susceptible RR-TB participants have been adjusted to 520 (including regimen A1, A2a, A3, A4 and A-SOC).

In fluoroquinolone-resistant RR-TB participants, we assume that 75% of participants in the experimental arm (regimen B1) and 65% of participants in the control arm (regimen B-SOC) will achieve a favourable outcome. A sample size of 82 per arm will afford 80% power to establish non-inferiority with a margin of 10% and a one-sided α level of 0.025. The number excluded from the modified intention-to-treat population is estimated to be 30% and therefore the recruitment target is increased to 117 per arm. The total sample size of fluoroquinolone-resistant participants is 234.

As of September 2025, enrolment for the fluoroquinolone-resistant group has completed, while recruitment of fluoroquinolone-susceptible participants remains ongoing.

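### The fixed sequence protects the group A non-inferiority tests, but not the superiority test added for every non-inferior regimen; read at one-sided 2.5%, the chance of a false superiority claim is about 5%

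*Protocol article*

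**What the plan says.** The section on sample size assumptions says that, because several regimens share one control, "the family-wise type I error will be controlled by a fixed sequence approach". The level follows: "All the previous comparisons will be done at the one-sided alpha level of 2.5" (per cent). The stopping rule there refers to non-inferiority alone: "if any group fails to demonstrate non-inferiority, testing for subsequent groups will be discontinued".

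The section on statistical considerations and analysis population makes the claim again without restricting it to non-inferiority: "Type I error rate will be controlled with a pre-planned fixed sequence method". The rule for moving on is "If non-inferiority is established, comparisons will proceed sequentially to the next experimental regimen in descending order of expected efficacy", and the paragraph ends with "For any regimen that demonstrates non-inferiority, a subsequent test for superiority over the control will be performed". Both questions would be read from one estimate: "The absolute between-group difference with 95% confidence interval (CI) in the proportion of participants with a favourable outcome will be calculated".

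The article gives no alpha for superiority, no order for those tests, and no statement on whether they fall inside the type I error control.

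**The concern.** A fixed sequence works because the full alpha travels along a single path and each test is reached only if the one before it succeeds. Here the path branches. When regimen k is shown non-inferior, testing moves to the non-inferiority of regimen k+1 whatever the superiority result for k, and the superiority of regimen k is tested as well. If both branches use the full 2.5%, the same alpha is spent twice at each step.

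For one regimen, non-inferiority followed by superiority needs no adjustment: the two hypotheses are nested and one confidence interval answers both. That argument does not carry over to several regimens when the alpha also passes to the next arm.

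At stake is a claim that a new regimen beats the national standard of care, made with less protection than a reader of the paragraph would assume. The design assumes 80% against 70%, so superiority results are a realistic outcome.

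**Working it through.** **Inputs from the protocol article.** One-sided 2.5% and a 95% interval; margin 10 points; 70% control and 80% experimental; 73 evaluable per arm (sample size assumptions). One shared control with 1:1 allocation to each arm (randomisation). Four experimental arms remain in group A: A1, A2a, A3 and A4.

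**Assumptions.** Superiority is tested at one-sided 2.5%, that is, the 95% interval excludes zero. The interval is the unpooled Wald interval, as the article names no method.

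**The plan's own figure.** The article states that "a sample size of 73 per arm will afford 80% power to establish non-inferiority of seven experimental regimens with a non-inferiority margin of 10" (per cent). Check: n = (1.960 + 0.842)² × (0.70×0.30 + 0.80×0.20) / (0.10 + 0.10)² = 7.849 × 0.37 / 0.04 = 72.6, so 73. Power at 73 is 80.2%. The figure reproduces.

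**Testing rule as written.** For arm k against control c:
- D_k = p_k − p_c, SE_k = √[p_k(1−p_k)/73 + p_c(1−p_c)/73], L_k = D_k − 1.96·SE_k (observed proportions).
- Non-inferiority of k is claimed if L_k > −0.10 and all earlier arms passed. This equals the article's rule on the upper bound when the difference is taken as control minus experimental.
- Superiority of k is claimed if non-inferiority of k was claimed and L_k > 0.

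**Results** (Monte Carlo, at least 400,000 runs, binomial arms, shared control; simulation standard error at 5.2% is √(0.052×0.948/400,000) ≈ 0.04 points):

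| True rates, 73 per arm | False non-inferiority | False superiority | Either |
|---|---|---|---|
| One arm, equal to 70% control | 0 | 2.7% | 2.7% |
| Two arms, equal to 70% control | 0 | 4.1% | 4.1% |
| Four arms, equal to 70% control | 0 | 5.2% | 5.2% |
| Four arms, equal to 80% control | 0 | 5.5% | 5.5% |
| Four arms, equal to 90% control | 0 | 6.4% | 6.4% |
| Arm 1 at 80%, arms 2 to 4 equal to 70% control | 0 | 4.7% | 4.7% |
| All four at the margin (60% v 70%) | 2.5% | 0.1% | 2.5% |

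The last row shows that the non-inferiority family is controlled. The first row shows that the Wald interval alone accounts for 2.7%. At a 70% control rate the branching therefore adds 5.2 − 2.7 = 2.5 points. With 104 evaluable per arm (nobody excluded from the modified intention-to-treat population) the four-arm figure at 70% is 6.0%.

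**Effect of a single chain.** Putting the superiority tests after all four non-inferiority tests, in the same order and stopping at the first failure, gives 1.1% when all arms equal a 70% control and 1.1% to 1.2% when only arm 1 is better. It stayed at about 2.5% or below in every case tried at 73 per arm.

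**The case against.** The strongest reply is that the article never claims to control superiority. The sample size section defines the sequence by non-inferiority, its 2.5% refers to those comparisons, and that control holds. The level and status of a follow-on superiority test could be set in an analysis plan that is not shown. Much of this stands, and several stronger readings that a reader might infer are not supported:

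- *The plan tests superiority at full alpha.* This is not written. It is the natural reading because 2.5% and the 95% interval are the only levels given, but it remains an assumption.
- *The claimed family-wise control fails outright.* It does not fail for non-inferiority.
- *Superiority lies wholly outside the sequence.* Each superiority test is gated by the regimen's own non-inferiority result and so by all earlier ones.
- *A false superiority claim is twice as likely as the plan says.* The plan states no probability for that error.
- *The error reaches 7.8%, or over 11%.* The first needs every non-inferiority gate to open. At 73 per arm and equal 70% rates, one gate opens about 26% of the time: 0.10/0.0758 = 1.32, and P(Z > 1.96 − 1.32) ≈ 0.26. The second also needs the superseded seven-arm design.
- *The case with arm 1 equal to control and the rest at the margin (about 4%) measures false superiority.* It mixes two errors; false superiority alone is 2.7% there.

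The trial is also powered for non-inferiority only. Superiority power at 80% v 70% is about 29%, and in the 5% scenario every regimen is truly as good as control. Falsely accepting a regimen 10 points worse would be the graver error, and that one is controlled.

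What the reply does not remove is that the statistical considerations section claims type I error control without restriction and, in the same paragraph, sets a superiority rule that is not marked as descriptive. Followed at the only level given, that rule does not deliver the control for superiority claims. This is a stated rule with a consequence, not only a missing detail.

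**Conclusion.** The point holds for the combined non-inferiority and superiority family in group A. With four arms and 73 evaluable per arm, the chance of at least one false superiority claim is about 5% when all arms equal control (5.2% to 6.4% for control rates of 70% to 90%) and about 4.7% when only the first arm is better than a 70% control. These figures rest on superiority being tested at one-sided 2.5% and on a Wald interval, and they vary with the true rates. The non-inferiority conclusions are protected at about 2.5%, and the group B comparison of B1 with its control is unaffected. Severity is moderate: the primary conclusions stand, but a superiority claim in group A would not carry the protection that the text implies.

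**What to change.** Choose one of two wordings while group A is still recruiting and before any comparative results are seen:

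1. **One chain.** Test non-inferiority of the four regimens in the pre-specified order, then superiority in that same order, each at one-sided 2.5%, stopping at the first failure.
2. **Restricted claim.** State that the family-wise control covers non-inferiority only, and report superiority as a descriptive 95% confidence interval with no confirmatory claim.

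Testing each superiority hypothesis at 0.025/4 while keeping the branch gave 1.7% to 2.5% in the scenarios tried at 73 per arm, but that is a check and not a proof of control, so it is not preferred.

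The cost is wording. Under the first option a formal superiority claim needs all four non-inferiority tests to succeed, so it is reached less often; under the second it is given up. Sample size and non-inferiority power do not change under either.
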